**Figure 4 fig4:**
[figure not shown]
Regions of interest and the channel setting.

During the formal test, the fNIRS device gives start and stop cues at corresponding time points, and the subjects are required to perform swallowing tasks according to the instructions issued by the device. The entire test process consists of 3 identical task blocks, each of which includes 30 s of voluntary swallowing task and 30 s of rest time. During the voluntary swallowing task, the subjects maintain a natural and relaxed state, close their eyes, and perform the repetitive saliva swallowing test task at their own pace.

During the rest period, the subjects are in a natural and relaxed state, close their eyes, remain quiet, and avoid thinking about things unrelated to the experimental task. The schematic diagram of the fNIRS voluntary swallowing task paradigm is shown in Figure 5 (25). The room is kept noise-free and free from external interference. Throughout the entire test process, the subjects always maintain a natural and relaxed state, close their eyes, and complete the corresponding tasks according to the instructions issued by the device. The head and body positions should be kept as still as possible to avoid affecting the fNIRS signal acquisition. Assessment time frames: at baseline; at week 6.

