For the analysis of fNIRS data, preprocessing will be conducted using the NirSpark software package (HuiChuang, China). Initial inspection of raw signals will be performed by an expert to exclude low-quality segments. Motion artifacts in each channel will be corrected through spline interpolation, targeting locally confined signal disruptions. Additionally, a band-pass filter (0.01–0.2 Hz) will be applied to attenuate physiological noise. Subsequent conversion to hemoglobin concentration changes in HbO2 and HbR concentrations will be carried out via the modified Beer–Lambert law (28). The hemodynamic response function (HRF) will be defined with a baseline period of 0–30 s and a task period spanning 30–90 s, extending the analysis window to 210 s. Generalized linear modeling will be applied to the HbO₂ and HbR time-series from each preprocessed dataset. Finally, hemoglobin time series covering 210 s will be extracted for every participant.

The hemoglobin time series for each channel pair will be analyzed using Pearson correlation. Given the normal distribution properties of the z-matrix, the resulting correlation coefficients (*r*) will be converted to *z*-scores using Fisher’s r-to-z transformation prior to further analysis. Based on Brodmann area (BA) classifications, measurement channels will be grouped into four regions: PFC, PM, S1, and M1. Taking into account the bilateral structure of the cerebral hemispheres, a total of eight distinct regions will be defined. An 8 × 8 functional connectivity matrix will then be constructed by independently averaging the z-scores, which will allow for the comparison of functional connectivity across networks.

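### The fNIRS task window is 60 s long although each block holds only 30 s of swallowing, so half of it is rest; the 210 s series also implies a lead-in that the task description does not mention

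*Protocol article*

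**What the plan says.** The fNIRS task is described under Secondary outcomes, in the text after Figure 4. There the whole test is "3 identical task blocks, each of which includes 30 s of voluntary swallowing task and 30 s of rest time". For a schematic of the paradigm the text refers to Figure 5. The same part of the article lists oxygenated and deoxygenated haemoglobin as a secondary outcome, measured both at rest and during voluntary swallowing.

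The analysis windows stand in the fNIRS paragraphs of Statistical analysis. The haemodynamic response function is defined with "a baseline period of 0–30 s and a task period spanning 30–90 s, extending the analysis window to 210 s". Linear modelling is then applied to the haemoglobin series, and the paragraph ends: "Finally, hemoglobin time series covering 210 s will be extracted for every participant". The next paragraph correlates the haemoglobin series of each channel pair, transforms the coefficients to z-scores and averages them into an 8 × 8 connectivity matrix. It does not say that the series is first divided into swallowing and rest.

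**The concern.** The two sections do not describe the same timeline. The task description gives 30 s of swallowing at a time, while the analysis section calls a continuous 60 s stretch the task period. An analyst who follows the analysis section literally would label rest as task and so shrink the estimated cortical response to swallowing.

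The analysis section also uses a recording longer than the three blocks that the task description calls the entire test. The reader cannot tell from the text what fills the remaining 30 s, or whether the 0–30 s baseline is really rest.

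Finally, correlating one undivided series mixes the states that the outcome definition names separately. Two channels that both respond to the task rise and fall together for that reason alone, so an arm difference in connectivity could partly reflect a difference in response size.

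At stake is the trial's neural measure, which the Discussion says was chosen to examine recovery of the swallowing network.

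**Working it through.** **Inputs**

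- Secondary outcomes: "The entire test process consists of 3 identical task blocks", and "each of which includes 30 s of voluntary swallowing task and 30 s of rest time".
- Statistical analysis: "a baseline period of 0–30 s"; "a task period spanning 30–90 s"; "extending the analysis window to 210 s".

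**Step 1: the 210 s figure**

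- Blocks alone: 3 × (30 + 30) = 180 s, which is 210 − 180 = 30 s short.
- The plan's own 0–30 s baseline placed before the blocks: 30 + 3 × 60 = 210 s, which reproduces the plan's figure exactly.
- A 30 s rest after the last block would also total 210 s, but then 0–30 s would lie inside the first block and would not be a separate baseline.

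**Step 2: content of the two windows**

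The task window is 90 − 30 = 60 s, which is one full block length. Seconds of swallowing and rest were counted in each window for six layouts:

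| Layout | Total | 0–30 s | 30–90 s |
|---|---|---|---|
| No lead-in, swallow first | 180 s | 30 s swallowing | 30 s swallowing + 30 s rest |
| No lead-in, rest first | 180 s | 30 s rest | 30 s swallowing + 30 s rest |
| 30 s lead-in, swallow first | 210 s | 30 s baseline | 30 s swallowing + 30 s rest |
| 30 s lead-in, rest first | 210 s | 30 s baseline | 30 s swallowing + 30 s rest |
| 30 s trailing rest, swallow first | 210 s | 30 s swallowing | 30 s swallowing + 30 s rest |
| 30 s trailing rest, rest first | 210 s | 30 s rest | 30 s swallowing + 30 s rest |

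The last column never changes, because the sequence repeats every 60 s and any 60 s window inside it holds one full cycle. The rest share of the task window is 30/60 = 50%.

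**Step 3: likely dilution**

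With true amplitude A during swallowing and 0 at rest, the window mean is (30 × A + 30 × 0)/60 = 0.50 A.

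The same question was put to a double-gamma response sampled at the plan's 11 Hz, with a 30 s lead-in and swallowing first:

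- mean of 30–90 s minus mean of 0–30 s: 0.50 of the true amplitude;
- 30–90 s as task regressor, fitted over 0–90 s: 0.54;
- all three 60 s blocks coded as task, fitted over 210 s: 0.52.

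The response shape and the coding are assumptions; the article states neither.

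**Step 4: what the 210 s correlation contains**

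With a lead-in, the series is 30 s baseline + 90 s swallowing + 90 s block rest = 210 s. All of it enters one coefficient per channel pair.

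**The case against.** **The 210 s length is not a true contradiction.** This largely stands. Adding the stated baseline to the three blocks gives 210 s exactly, and Figure 5 may show the lead-in. What remains is that the prose calls the three blocks the whole test and names no lead-in.

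**The task period may mean the first full response epoch, task plus recovery.** This is possible, since 30–90 s is exactly one block if there is a lead-in. The text does not say so. It sets a baseline period against a task period and defines the response function with them, so the wording needs correcting even on this reading.

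**The size depends on an unstated design matrix.** This stands, and the figure of about one half is therefore only illustrative. If 30–90 s were the only task epoch coded in the whole 210 s, the same calculation would give 0.10, but nothing in the article says that the second and third blocks go uncoded. Any attenuation would also apply in every arm, so it costs sensitivity without favouring one arm.

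**Stronger readings.** A reader might infer that swallowing is used as baseline and that the activation estimate could change sign. That needs 0–30 s to be swallowing, as in a recording that opens directly with a swallowing period. Without a lead-in such a recording lasts 180 s unless 30 s is added at the end, and the exact 30 + 180 match argues against it. A reader might also infer that the connectivity values mostly reflect shared task timing. A simulated correlation of 0.51 has been computed for two channels with independent noise and a shared response of equal variance. That value follows from the assumption, because the expected correlation is 1/(1 + 1) = 0.5, and the article gives no basis for that variance ratio.

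**Detail on regressors and segments belongs in a fuller document.** This is fair for what is left out. It does not cover a 60 s window that the article states and that disagrees with its own 30 s task.

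**Conclusion.** The point holds in a limited form. The mismatch between a 60 s task window and a 30 s task is certain from the text: half of the window is rest in every layout examined. Used as the task regressor or averaging window, it would dilute activation to roughly half (0.50 to 0.54), assuming a canonical response, a 30 s lead-in with swallowing first, and one of the codings shown above.

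The 210 s length is an omission to be cleared up. It most probably reflects a 30 s pre-task rest, which the task description leaves out and which could not be confirmed without Figure 5. The documents do not establish swallowing as baseline, a reversed sign or a quantified bias in connectivity. They do show that the correlation, as described, pools baseline, swallowing and rest.

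The matter is worth correcting before the data are analysed. It concerns one secondary mechanistic outcome in a pilot trial; the FOIS analysis and the sample size are untouched.

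**What to change.** 1. Reconcile the task description with the analysis section. If a 30 s pre-task rest is recorded, state it in the task description. If it is not, shorten the series to 180 s and take the baseline from rest.
2. Code the task from the recorded markers as the actual 30 s swallowing periods. With a lead-in and swallowing first these are 30–60, 90–120 and 150–180 s, and the remaining segments are rest.
3. Compute connectivity separately for swallowing and rest, or on residuals after the modelled task response is removed, at least as a sensitivity analysis beside the 210 s correlation.

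The cost is a wording change and a change to the analysis script; the recordings stay as they are. The drawback is that shorter segments give noisier correlations, which is one reason why the third item may be kept as a sensitivity analysis.

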### Ethics and dissemination

This study has been approved by the Medical Ethics Committee of the Third Affiliated Hospital of Zhejiang Chinese Medical University (ethical number: ZSLL-KY-2024-074-01). Informed consent will be obtained from each patient before the performance of any study-specific procedure. Personal information about potential and enrolled participants will be protected and strictly confidential before, during, and after the trial. Data of the results without personal information from this study will be planned to disseminate in conferences or peer-reviewed publications.

## Discussion

This manuscript presents the design of a randomized controlled pilot trial testing the effectiveness and safety of SMES combined with NGF to improve dysphagia after ischemic stroke. To the best of our knowledge, there is no published literature on the effectiveness of SMES combined with NGF for dysphagia after ischemic stroke.

Dysphagia, one of the most common complications of stroke, is characterized by impaired swallowing efficacy (leading to malnutrition and dehydration) and compromised swallowing safety (increasing risks of aspiration and aspiration pneumonia) (1). Even with the most effective rehabilitation strategies, satisfactory outcomes may not always be achievable. In this design, we apply an alternative approach for NGF delivery to enhance the clinical efficiency. Based on our previous achievements, SMES is a convenient and effective approach to open the BBB in a controllable and reversible manner. Building on standard swallowing training, SMES may facilitate NGF delivery across the BBB and promote swallowing network plasticity. The concept of opening the BBB is absent in traditional acupuncture theory; thus, SMES represents an innovation beyond conventional acupuncture. SMES holds significant promise for drug delivery across the BBB to treat brain diseases (12, 29).

There are numerous clinical studies on NGF therapy for peripheral nerve injury (30). However, its application in central nervous system disorders has been limited by the BBB. By opening the BBB, SMES may enable NGF to reach brain targets, potentially improving swallowing function after stroke. Nevertheless, randomized controlled trials (RCTs) are needed to validate this combined intervention. The present study aims to provide preliminary evidence for its clinical application.

Regarding outcome measures, the primary outcome is the FOIS, a validated tool for assessing global swallowing capacity. Secondary outcomes include the DOSS, which evaluates swallowing efficiency and safety; the PAS, which focuses on aspiration risk (19); the mRS, which measures post-stroke functional recovery; and the MBI, which assesses activities of daily living.

Multimodal findings from clinical, electrophysiological, and imaging studies suggest that dysphagia recovery after stroke involves neuroplastic changes in the contralesional hemisphere across sensory, motor, and white matter domains (31–39). This body of evidence supports a compensatory model of contralesional neuroplasticity as the driving mechanism for recovery (1). fNIRS and electroencephalography (EEG) are two convenient brain function imaging techniques that have attracted significant attention in recent years and have yielded numerous significant findings on the mechanism of acupuncture’s effects on the brain (14, 40–42). Currently, the application of EEG in the study of PSD remains limited, but many fNIRS studies have proved that the effect of acupuncture can upregulate activation patterns in the cortical swallowing network and strengthen functional integration among specific regions (14). This study is not focused on the direct cerebral effects of acupuncture. Instead, fNIRS was chosen as the research method to examine the swallowing network recovery induced by NGF. In terms of study design, the four-arm study can highlight the interaction effect between SMES and NGF, and distinguish it from the independent effect of acupuncture at the GV20 and GV26 acupoints.

In China, a significant proportion of PSD patients have prior acupuncture experience, making patient blinding challenging (43). Thus, conventional acupuncture rather than sham acupuncture will serve as the control to optimize blinding feasibility.

There are some limitations to our study. First, as a pilot trial, the sample size is relatively small, which may increase susceptibility to bias. Second, acupuncturists could not be blinded due to the nature of the intervention, potentially introducing performance bias. Third, future studies should incorporate pharmacokinetic sub-studies to optimize the timing between NGF administration and SMES stimulation. Fourth, the SMES parameters (2/100 Hz, 3 mA, 6 s-on/6 s-off) were derived from rodent models. Given biophysical differences between species (e.g., impedance, skull geometry), the intracranial current density in humans requires empirical validation. Future research should use computational modeling, neuroimaging (e.g., dynamic contrast-enhanced MRI), or electrophysiological monitoring for systematic dose-finding. Fifth, while the factorial design distinguishes SMES-specific effects from traditional acupuncture, any observed superiority of SMES + NGF would require confirmation in future trials with strict sham controls and biomarkers before attributing it definitively to BBB-mediated NGF delivery. Sixth, a negative or null result could reflect two distinct possibilities: (1) lack of biological efficacy of the combined intervention, or (2) suboptimal temporal alignment between NGF availability and BBB opening, despite a potentially efficacious mechanism. The current design cannot distinguish between these. Thus, a negative result would highlight the need for further pharmacokinetic-pharmacodynamic studies to optimize intervention timing before concluding on biological plausibility.
